#### Qualitative interviews

We will use qualitative methods to understand HCWs barriers and motivators for influenza vaccine uptake and policy makers’ perspectives on influenza vaccination feasibility. The qualitative methodologies will be in-depth interviews (IDIs) and focus group discussions (FGDs) among vaccinated and nonvaccinated HCWs. We will also conduct key informant interviews (KIIs) among policy makers.

For planning purposes, we anticipated a minimal sample size for each target group to reach saturation (Table 1 and Table 2), based on experiences from previous studies. This indicates a minimal sample size (Table 1 and Table 2). However, participants will be recruited until theoretical saturation for the research objective is reached, which is the point when no new insights are generated through the data.

**Table 1 Tab1:** Sample size and sample distribution for in-depth interviews (IDI) and focus group discussions (FGD)

Type of interview method and selection criteria	Category	Target group	No. of the interview in each facility	Total no. of interviews in four hospitals
In-depth interviews (IDIs) participant selection (participants will be selected from years of experience, the domain of expertise and male: female ratio will be maintained)	Vaccinated	With doctors	1	4
		With nurses	1	4
		With allied health personnel	1	4
	*Nonvaccinated*	With doctors	1	4
		With nurses	1	4
		With allied health personnel	1	4
	**Total number of IDI participants**			**24**
Focus group discussions (heterogeneous in the combination of male–female participation; 8–10 participants in each discussion)	Vaccinated	With intern doctors		1
		With nurses		1
		With allied health personnel		1
	*Nonvaccinated*	With intern doctors		1
		With nurses		1
		With allied health personnel		1
	**Total number of FGDs**			**6**

**Table 2 Tab2:** Sample size and sample distribution for key informant interviews (KIIs)

Target group	Number of KIIs
Director, Communicable Disease Control, Directorate General of Health Services(DGHS)	1
Director, IEDCR, DGHS	1
Line Director, EPI	1
Program manager, EPI	1
Deputy program manager, EPI	1
Key personnel from WHO	1
Current and retired influenza experts	2
Members of the National Immunization Technical Advisory Group (NITAG)	2
GAVI Bangladesh	1
Hospital directors	4
**Total number of interviews**	**15**

### Intervention

The intervention activities will be started before the influenza season, from May to September, in Bangladesh. Before the start of the influenza season, the study hospitals (4) will be randomly allocated into four study arms: (1) ensuring availability of influenza vaccine, (2) increasing influenza vaccination awareness, (3) ensuring the supply of influenza vaccine, and increasing awareness of influenza vaccine simultaneously (4) control arm with no intervention. We will take the following measures for specific arms of intervention hospitals to inform study participants about receiving influenza vaccination.

### Intervention arm-1: Intervention package with the availability of vaccine supply only

1.1. In Bangladesh, vaccine suppliers sell inactivated, quadrivalent influenza vaccines in both the Northern and Southern Hemisphere compositions of the vaccine [33]. The reason behind the availability of these vaccines is that Bangladesh is located in the tropical and subtropical southern and south-eastern Asia region, and country-specific data suggest that peak influenza activity occurs from May to September [34–36]. This vaccine contains influenza A(H3N2), pandemic A(H1N1) 2009 subtypes, and influenza B lineages B/Yamagata and B/Victoria. We will work with private suppliers to ensure vaccines are available at the hospital premises. Then a vaccination booth will be set up at the hospital premises, and administer the vaccine at the market-rated price (MRP). The booth will be open during the two-month intervention period and from 9 AM to 2 PM during each working day.

1.2. All HCWs will be notified about only vaccine availability information by the hospital director and respective department heads.

1.3. A list of all staff working in the study hospitals will be prepared, and they will be provided with an influenza vaccination record card with a unique identification number. The study staff will ensure receipt of vaccination cards for all participants.

1.4. A short message (SMS) will be delivered over the mobile phone number to all participants, e.g., vaccination program duration, venue, time, and vaccine price, to cascade vaccination information to participants.

1.5. Posters with only vaccine delivery information (i.e., vaccination duration, vaccination venue, vaccine price) will be displayed at key hospital locations, e.g., the main entrance of the hospital, nursing station, vaccine delivery point/place, doctors’ room, nurses’ room, intern doctors’ room, common room canteen, etc.

### Intervention arm-2: Intervention package with vaccination awareness only

2.1. The hospital director and respective heads will notify all HCWs about participating in the vaccination awareness program facilitated by the study team.

2.2. We will arrange separate seminars for each group of HCWs (doctors, nurses, and allied health personnel) in the hospital to sensitize participants about the significance of receiving influenza vaccines and the risk and benefits of influenza vaccination.

2.3. A list of all staff working in the study hospitals will be prepared, and they will be provided with an influenza vaccination record card with a unique identification number. The study staff will ensure receipt of vaccination cards for all participants.

2.4. A SMS will be delivered over the mobile phone number to all participants, e.g., time to vaccinate, vaccine price, and available places to purchase the vaccine.

2.5. Posters containing messages on the importance of influenza vaccination will be displayed at key hospital locations, e.g., the main entrance of the hospital, nursing station, vaccine delivery point/place, doctors’ room, nurses’ room, intern doctors’ room, common room canteen, etc. All the material will be adopted and contextualized from the available literature [37–39]. Figure 3 depicts the information delivery mechanism.

2.6. No vaccination booth will be set up at the hospital premises.

### Intervention arm-3: Intervention package with a combination of vaccine availability and awareness

3.1. We will work with the study hospital authority, influenza vaccine manufacturer, and supplier company to set up a vaccination booth at the hospital premises to administer the vaccine at the MRP by hospital nurses.

3.2. The hospital director and respective department heads will notify all HCWs to receive the offered influenza vaccine.

3.3. A list of all staff working in the study hospitals will be prepared, and they will be provided with an influenza vaccination record card with a unique identification number. The icddr,b, study staff will ensure receipt of vaccination cards for all participants.

3.4. We will arrange separate seminars for each group of HCWs (doctors, nurses, allied health personnel) in the hospital to sensitize participants about the objectives and implementation of the ongoing vaccination program as well as about the significance of receiving influenza vaccine and the risk and benefits of influenza vaccination.

3.5. A SMS will be delivered over the mobile phone number to all participants, e.g., vaccination program duration, venue, time, and vaccine price, to cascade vaccination information to optimum participants.

3.6. Posters with key messages will be displayed at crucial hospital locations, e.g., the hospital's main entrance, nursing station, vaccine delivery point/place, doctors’ room, nurses’ room, intern doctors’ room, common room canteen, etc.

### Control arm: No intervention

4.1. In the control facility, we will not intervene in the existing knowledge and practice about influenza vaccination of the HCWs.

### Implementing the vaccination program (for intervention arms 1 & 3)

A vaccination booth will be set up at the nurse’s station or in a common space in both hospitals. The vaccine will be provided at MRP among HCWs. The hospital nurses will administer the vaccine. After receiving the vaccine, HCWs will sign the vaccination card in front of the staff nurse to ensure receiving the vaccine receipt. During the two-month vaccination program, icddr,b staff will monitor the entire program and ensure vaccine and logistics availability in study hospitals.

To report any adverse events following immunization (AEFI), we will follow the existing surveillance channels established by the WHO and the MoHFW, the Government of Bangladesh. During the intervention briefing session at each study arm, we will provide information about reporting an AEFI (if any) within the hospital’s existing surveillance system as well as the hotline number (provided in the consent form) to inform such issue. Moreover, an icddr,b staff will be placed at each study hospital throughout the study implementation period. He/she will also monitor any AEFI issue and existing hospital surveillance setup. If any AEFI case is found, the icddr,b staff will immediately inform the Hospital Surveillance Officer (HSO), assist the HSO in filling in the AEFI report form, and submit it to the Expanded Programme on Immunization (EPI) headquarter through the Chief Health Officer. Besides, we will analyze the AEFI data (i.e., the number of AEFI reports received, number of AEFI by type, and classification of AEFI by cause) and share the findings with key stakeholders, including the Directorate General of Drug Administration (DGDA).

### Quantitative data collection

We will employ a quantitative method for evaluating the effect of the intervention. We will perform the following activities:

5.1. We will conduct a baseline survey among HCWs of the study hospitals to collect information on HCWs’ influenza vaccine uptake history and their knowledge and perception of influenza vaccination.

5.2 At the end of the influenza vaccine season, we will do a post-intervention survey at study facilities to collect similar information.

Trained staff will approach the participants to solicit their interest and consent. The staff will be well-spoken and discuss with the study participants regarding confidentiality, objectives of the survey, use of data, and utility of results. Those who agree to participate will be interviewed according to the survey questionnaire. The structured questionnaire will be developed and contextualized following a review of the literature from prior research [40–44]. The questionnaire will be focused on the number of vaccinated HCWs (evidence from the signed vaccination card), socio-demographic information of the participants, including age, gender, profession (doctor/nurse), and department; perception of influenza risk; perception of vaccine effectiveness and side effects, practices of recommending vaccination to family and patients, and practice and attitude towards a mandatory vaccination and their willingness to pay for future vaccination.

### Qualitative data collection

At the end of the intervention, qualitative interviews will be conducted. IDIs and FGDs will be used to understand vaccinated and nonvaccinated participants’ perceptions about influenza risk, vaccine effectiveness, side effects, and adverse effects. IDIs will be performed with both vaccinated and non-vaccinated HCWs to reveal an in-depth understanding of the factors and decisions for participating in vaccination. In addition, we will conduct FGDs with intern doctors (to understand group behavior and peer pressure on vaccination), nurses, and allied health personnel for data triangulation and comprehend the influence of group behavior on vaccine uptake.

To explore the feasibility of the influenza vaccination of HCWs, we will collect qualitative data through KIIs with purposively selected personnel and stakeholders. The qualitative data will be on experiences with influenza vaccination programs; barriers faced in implementing the vaccination program; existing workload; availability of infrastructural supports, logistics, and human resources; adequacy of cold chain and vaccine storage management; suitability of vaccination session management; and assessment of previous vaccination programs among health workers (if any), with particular attention to the feasibility of influenza vaccination among HCWs. We will summarise the interview data to prepare a policy brief and share it with the National Immunization Technical Advisory Group (NITAG).

### Data analysis

#### Quantitative data

We will conduct descriptive analysis to summarise the categorical variables using frequency, percentage, and 95% confidence interval (CI). We will summarise numerical or continuous variables using mean and standard deviation (SD) for symmetric distribution and median and interquartile range (IQR) for asymmetric distribution. We will estimate the Difference in Differences (DID) with 95% CI of the proportion of vaccine uptake between each intervention and control (non-intervention) arm, adjusting for the clustering effect and testing whether it is statistically significant or not at a 5% level of significance. We will also look for association and estimate the odds ratio (OR)/risk ratio (RR) with 95%CI between influenza vaccine uptake and its barriers and motivators, adjusting for clustering effect and covariates using multiple logistic regression/multilevel models.

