There is currently no national influenza vaccination strategy in Bangladesh for the population at increased risk of influenza-like-illness such as HCWs, as recommended by WHO [30]. Each year, the Ministry of Health and Family Welfare (MoH&FW) of the People's Republic of Bangladesh provides free influenza vaccination to all Hajj pilgrims as a mandatory requirement imposed by the Saudi Health Ministry; this is the only group in Bangladesh that has a seasonal influenza vaccine policy [31]. Currently, only a few selected private vaccination centers in Dhaka offer influenza vaccines at a market-rated price (MRP). However, the number of doses administered per year by private vaccination centers remains unknown**.** Due to the limited availability of the vaccine in Bangladesh, the willingness to receive the influenza vaccine of risk group populations such as HCWs remains unclear.

To protect HCWs and reduce nosocomial influenza transmission in both epidemic and pandemic settings, the promotion of influenza vaccination for this risk group should be a priority. HCWs’ knowledge, attitudes, and perceptions about influenza and influenza vaccine influence their decision regarding vaccination. Understanding the barriers and motivation of vaccine uptake is required to tailor local influenza vaccination policies and implementation strategies to facilitate and improve vaccine uptake.

This study intends to determine the current status of influenza vaccination among HCWs and generate preliminary data on whether increased awareness and availability of influenza vaccine improve vaccine uptake and factors affecting the uptake rates. The critical data generated from the study would inform the development of an influenza vaccination policy for HCWs.

We hypothesize that increasing awareness and availability of influenza vaccine supply would increase influenza vaccine uptake among Bangladeshi HCWs. We formulated the research questions (RQ): What are the effects of influenza vaccination awareness or availability of vaccine supply or both in the study hospitals on HCWs' influenza vaccine uptake in Bangladesh?

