### Study design

We will use a cluster randomized controlled trial design with the hospital as the unit of randomization and intervention. The four different types of intervention will be randomly allocated and implemented in four study hospitals separately. The four interventions will be: 1^st^ intervention: ensuring availability of influenza vaccine supply; 2^nd^ intervention: developing influenza vaccine awareness activities; 3^rd^ intervention: both ensuring the availability of influenza vaccine supply and developing influenza vaccine awareness activities, and 4^th^ intervention: control arm with no intervention. We will assess influenza vaccine uptake before and after intervention and between different study arms. Moreover, barriers and motivators of vaccine uptake will be explored by applying both quantitative surveys and qualitative methods (i.e. in-depth interviews and focus group discussions)
. We will also use a qualitative approach (i.e. key informant interviews) to understand the policymakers’ (such as hospital administration, influenza vaccine expert) perspectives and opinions on influenza vaccine uptake among HCWs. Figure 2 & Fig. 3 illustrates the study design and interventions.

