### Sample size and sampling

#### Quantitative survey

Our primary outcome of interest is influenza vaccine uptake among HCWs. An ongoing study among HCWs in Bangladesh at tertiary level facilities has shown a baseline influenza vaccine uptake of about 5% ([name] et al., personal communication). But comprehensive reviews on influenza vaccine uptake among HCWs have identified a wide variation of vaccine uptake rates globally between 13–53% [26]. We expect a similar uptake rate between 10–50% following awareness and availability of influenza vaccine supply in study hospitals. However, we assume an increase in the uptake rate of at least five percentage points for the sample size requirement.

For a one-sided test, given the allocation ratio R = n_2_/n_1_, the total sample size n is computed by the following formula:$$n=\frac{{\left\{{z}_{1-\alpha \sqrt{\overline{p }\left(1-\overline{p }\right)}-{z}_{\beta }\sqrt{{w}_{2}{p}_{1}\left(1-{p}_{1}\right)+{w}_{1}{p}_{2}\left(1-{p}_{2}\right)}}\right\}}^{2}}{{w}_{1}{w}_{2}{\left({p}_{2}-{p}_{1}\right)}^{2}}$$

where uptake rate p_1_ = 5% in the control group and p_2_ = 10% in the intervention group, the pooled proportion $$, \overline{p }$$ = (n_1_p_1_ + n_2_p_2_)/(n_1_ + n_2_), and w_1_ = 1/(1 + R) and w_2_ = R/(1 + R). (Stata 13 manual; page 156). In our case, R = 1 for equal allocation, Z_1-α_ = 1.645 for 5% level of significance and Z_β_ = 0.84 for 80% power.

The estimated sample size is 435 HCWs in each arm. With a clustering (design) effect of 2 and a 10% non-response rate, a sample size of 957 HCWs is required for each arm. Consequently, the total sample size is 3,828.

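### With one hospital per arm, the planned cluster-adjusted 5% test and the 80% power cannot be delivered for the intervention effect

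*Protocol article*

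**What the plan says.** - Protocol article, Study design: "We will use a cluster randomized controlled trial design with the hospital as the unit of randomization and intervention". The same section adds: "The four different types of intervention will be randomly allocated and implemented in four study hospitals separately". The Intervention section confirms that "the study hospitals (4) will be randomly allocated into four study arms". That is one hospital per arm.
- Sample size and sampling, Quantitative survey: uptake of 5% against 10%, 435 per arm, then "With a clustering (design) effect of 2 and a 10% non-response rate, a sample size of 957 HCWs is required for each arm", for a total of 3,828. The stated error rates are "1.645 for 5% level of significance and Z_β_ = 0.84 for 80% power". The section gives no intracluster correlation (ICC) and does not say which level of clustering the design effect describes.
- Data analysis, Quantitative data: DID with a 95% CI for each intervention arm against control, "adjusting for the clustering effect and testing whether it is statistically significant or not at a 5% level of significance".
- Background: the study is meant to "generate preliminary data on whether increased awareness and availability of influenza vaccine improve vaccine uptake". Nothing in the article says that hospital and arm coincide or limits the comparison to description.

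**The concern.** A cluster-adjusted standard error needs replication of the unit that was randomised. Here no arm has any. A hospital's uptake can move between the surveys for reasons of its own, and that movement cannot be told apart from the effect of the arm the hospital was given. A p-value or CI built only from variation among health workers leaves this component out, yet it would be read as inference about the intervention. The Conclusion section says that findings go to the national immunisation advisory group and the ministry for policy decisions, so an overstated claim on the primary outcome would carry weight.

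**Working it through.** **1. The plan's own figures.** With p1 = 0.05, p2 = 0.10 and mean 0.075, n per arm = [z_α·√(2·0.075·0.925) + z_β·√(0.05·0.95 + 0.10·0.90)]² / 0.05². Two-sided 5% and 80% power give 435, the printed figure. The section describes a one-sided test with z = 1.645, which gives 343. That mismatch is a separate matter, and the calculations below are two-sided because 435 is. Then 435 × 2 × 1.10 = 957 and 957 × 4 = 3,828, as printed. The number of respondents behind the power claim is 435 × 2 = 870 per hospital. Reading 10% non-response as 957 × 0.90 ≈ 861 changes nothing material.

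**2. Degrees of freedom.** Four hospitals at two surveys give 8 cell proportions. The DID model has 4 hospital terms + 1 period term + 3 arm-by-period terms = 8 parameters of rank 8, so residual df = 8 − 8 = 0. Adding hospital-by-period terms leaves the rank at 8: they are fully aliased with the intervention effects. In simulated data with 870 per cell, standard errors clustered on hospital collapsed to about 10⁻¹⁶, against 0.0150 for the individual-level DID standard error. They give no usable interval or test.

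**3. What the design effect of 2 would imply.** If it refers to hospitals, 1 + (870 − 1)·ICC = 2, so ICC = 1/869 ≈ 0.0012. At 5% uptake this is a between-hospital SD of √(0.00115 × 0.05 × 0.95) ≈ 0.7 percentage points (pp). This trial cannot check that value.

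**4. Randomisation inference.** For one intervention-control pair, with the other arms free to have effects, only 2 allocations exchange the pair, so the smallest one-sided p is 1/2. Under the null of no effect in any arm, all 4! = 24 allocations count and 2 of them give the most extreme pairwise contrast: p = 2/24 = 1/12 = 0.083 one-sided. Neither reaches 5%.

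**5. Illustration of size.** Assumptions, none of them given in the article: independent samples at the two surveys, and hospital-specific drift between surveys with SD t.

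- Null sampling SE of the DID = √(4 × 0.05 × 0.95 / 870) = 1.48 pp.
- Total SE = √(1.48² + 2t²).
- False-positive rate = 2[1 − Φ(1.96 × 1.48 / total SE)]. With the design effect of 2, 1.48 is multiplied by √2 inside the bracket.
- For power, the sampling variance is (3 × 0.05 × 0.95 + 0.10 × 0.90)/870, so the SE is 1.63 pp. Power = Φ(5/√(1.63² + 2t²) − 1.96), treating the drift variance as known.

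| Drift SD t (pp) | Total SE under null (pp) | False positives, individual-level SE | False positives, SE × √2 | Power for a 5 pp effect |
|---|---|---|---|---|
| 1 | 2.05 | 16% | 4.5% | 64% |
| 2 | 3.19 | 36% | 20% | 33% |
| 3 | 4.49 | 52% | 36% | 20% |

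**The case against.** - **DID deals with hospital differences.** It does for stable ones. Hospital-specific change remains, and that is the aliased part.
- **Clustering may mean departments or staff groups.** The sample-size and analysis sections name no level, so the ICC of 0.0012 holds only if hospitals are meant and should not be attributed to the authors. Adjusting within hospitals would give a number, but not replication at the level that was randomised.
- **Drift may be small.** The Background says the vaccine is sold only at a few private centres in Dhaka, the study hospitals are elsewhere, and assumed baseline uptake is about 5%. This is a fair point. At a drift SD of 1 pp, the standard error inflated by the design effect keeps the error rate near nominal. A reader might infer that the 5% test must be badly inflated; the documents do not show that, because they give no drift SD. Nor can the trial show which row of the table applies.
- **A large effect would be visible anyway.** This also stands. The article expects uptake of 10–50%. A rise from 5% to 30% with a drift SD of 3 pp has sampling variance (3 × 0.05 × 0.95 + 0.30 × 0.70)/870, a total SE of about 4.7 pp, and z ≈ 25/4.7 ≈ 5. A reader might conclude that the trial can show nothing; that goes too far. The damage is greatest near the 5-point effect used for sizing.
- **The study is called preliminary.** It is, in the Background. That word does not withdraw the power claim or the significance test, and it does not disclose the confounding.
- **Some randomisation test might reach 5%.** A prespecified ordering of all four arms could give 1/24 = 0.042, but the plan is for pairwise contrasts.

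**Conclusion.** The point stands as a structural one and needs no assumed value: with one hospital per arm, hospital-by-time variation has zero degrees of freedom. The cluster adjustment at the randomised level, the 5% test and the 80% power are therefore not properties of this design for the intervention effect. A separate analysis plan could not supply the missing replication. The sizes (false-positive rates of 16%, 36% or 52%, or 4.5%, 20% or 36% with the design effect; power of 64%, 33% or 20%) are illustrations. They rest on the assumed drift SDs, on independent surveys (the article does not settle whether the same workers are interviewed twice) and on 870 respondents per hospital and survey.

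Two stronger readings should be avoided. The figure of 1/12 is not the smallest p-value for a planned contrast taken alone; it needs the null of no effect in any arm. And power computed from cross-sectional ICCs for a post-survey comparison does not describe this plan, because DID cancels the stable part of that variance.

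**What to change.** 1. **Sample size and sampling, Quantitative survey:** withdraw the claim of 80% power for the intervention effect and describe 957 per arm as giving precision within each hospital.
2. **Data analysis, Quantitative data:** report each DID with a 95% CI labelled as conditional on these four hospitals and excluding hospital-by-time variation. Drop the 5% significance claim for the intervention effect. Add a sensitivity table using √(SE² + 2t²) with t = 1, 2 and 3 pp. On the null SE above, the 95% half-width goes from 1.96 × 1.48 = 2.9 pp to 1.96 × 2.05 = 4.0, 1.96 × 3.19 = 6.3 and 1.96 × 4.49 = 8.8 pp.
3. **Study design, Discussion and Conclusion:** describe the trial as an unreplicated one-hospital-per-arm comparison giving preliminary data, and word conclusions as differences between these hospitals.
4. **Optional:** use whatever past-season vaccination history the baseline survey already holds to gauge drift. New baseline items should not be relied on, since the Trial registration section dates the first enrolment to March 2022.

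The cost is a change of wording and one added table, with no more hospitals or participants. The downside is a weaker claim.

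### The primary difference-in-differences names adjustment for clustering only, leaving it open to hospital-specific changes in respondent mix and to profession-specific time trends

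*Protocol article*

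**What the plan says.** The primary outcome is fixed under Sample size and sampling, Quantitative survey: "Our primary outcome of interest is influenza vaccine uptake among HCWs". Its analysis is under Data analysis, Quantitative data: "We will estimate the Difference in Differences (DID) with 95% CI of the proportion of vaccine uptake between each intervention and control (non-intervention) arm", continuing "adjusting for the clustering effect and testing whether it is statistically significant" at the 5% level. The Method paragraph of the abstract repeats the DID with the same clustering-only adjustment.

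The following sentence of the Data analysis section concerns a different analysis, the association of uptake with barriers and motivators. There the plan is "adjusting for clustering effect and covariates using multiple logistic regression/multilevel models".

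The questionnaire records "socio-demographic information of the participants, including age, gender, profession (doctor/nurse), and department" (Quantitative data collection). Study population and participant recruitment defines three staff categories: doctors, nurses and allied health personnel.

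On design, "The four different types of intervention will be randomly allocated and implemented in four study hospitals separately", so each arm is one hospital. On timing, "We will conduct a baseline survey among HCWs of the study hospitals", followed by a post-intervention survey. The article does not say whether the same people answer both surveys.

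**The concern.** Adjusting for clustering addresses the variance of the estimate, not who the respondents are. With four hospitals and four arms, randomization cannot balance staff mix. Participation depends on consent at each survey, and no stratification of the sample by profession is stated. If the respondents in one hospital shift towards a group with higher uptake between surveys, an unadjusted DID counts that shift as intervention effect. The same happens if uptake rises over time mainly in one profession and the hospitals employ that profession in different proportions.

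The article states an adjustment for the primary estimate twice without covariates, and names covariates only for the secondary model. The point is therefore about a stated method as well as about missing detail.

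**Working it through.** **Planning figures.** The article takes 5% uptake against 10%, a difference of 5 points. Its 435 per arm is reproduced by the pooled-variance formula for two proportions with a two-sided 5% level and 80% power. The printed one-sided value of 1.645 gives 342 to 343, but that mismatch is a separate matter. Then 435 × 2 = 870, 870 × 1.10 = 957 and 957 × 4 = 3,828, as printed. Covariate adjustment changes none of these figures.

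**Inputs assumed for illustration.** The protocol gives no uptake by profession and no staff mix. Assume doctors/nurses/allied of 50/30/20% in the intervention hospital and 30/40/30% in control. Assume uptake of 10/5/2%, with a range from 8/5/3% to 15/5/2%. Hospital uptake is the sum of share × rate, and there is no intervention effect.

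**(a) Mix differs between hospitals but is stable.**
- Intervention: 0.5 × 10 + 0.3 × 5 + 0.2 × 2 = 6.9%
- Control: 0.3 × 10 + 0.4 × 5 + 0.3 × 2 = 5.6%
- The cross-sectional gap is 1.3 points at both surveys, so DID = 1.3 − 1.3 = 0.

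**(b) The same shift in both hospitals.** The change is equal in each, so DID = 0.

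**(c) Shift from allied staff to doctors in one hospital only.** Bias = shift × (doctor rate − allied rate).

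| Uptake, doctors/nurses/allied | Gap | 5-point shift | 10-point shift | 20-point shift |
|---|---|---|---|---|
| 8/5/3% | 5 | 0.25 | 0.5 | 1.0 |
| 10/5/2% | 8 | 0.4 | 0.8 | 1.6 |
| 15/5/2% | 13 | 0.65 | 1.3 | 2.6 |

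**(d) Mix stable, trend differs by profession.**
- Doctors rise 5 points, others none: 0.5 × 5 − 0.3 × 5 = 1.0 point.
- Doctors rise 10 and nurses 2: (5.0 + 0.6) − (3.0 + 0.8) = 1.8 points.
- An equal rise in all groups: 0.

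**How large a shift is plausible?**
- Chance alone: with 870 respondents per survey, simple random sampling and stable staffing, the standard error of a change in doctor share is at most √(2 × 0.25/870) = 2.4 points. A 10-point shift is more than 4 standard errors.
- Non-response at the planned 10%: if doctors are 40% of staff and every non-respondent is a non-doctor, their share becomes 0.40/0.90 = 44.4%. Treated as a swap of doctors for allied staff, that 4.4-point shift is worth about 0.044 × 5 = 0.2 to 0.044 × 13 = 0.6 points.

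**Precision.** Take 5% uptake, 30% doctors and a 10-point gap. Profession explains 0.3 × 0.7 × 0.10² = 0.0021 of a variance of 0.05 × 0.95 = 0.0475, or 4.4%. The individual-level standard error falls by 1 − √(1 − 0.044), about 2%.

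**The case against.** A reader might infer that any difference in staff mix between hospitals passes into the effect estimate. It does not: cases (a) and (b) give zero, because removing stable differences is what a DID does.

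A reader might also take shifts of 10 to 15 points in doctor share as ordinary. Under random selection from a staff list with about 10% non-response they are unlikely. They would need real staffing change or a breakdown in response, and the article indicates neither. If the same staff answer both surveys, mix changes only through attrition or differential non-response, and the article leaves this open. A 20-point doctor/other gap at 5% overall uptake is possible only if doctors are at most 5/20 = 25% of staff and nobody else is vaccinated. Larger gaps are possible after intervention, when the article expects 10 to 50% uptake.

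The strongest objection concerns scope. The article is condensed, a covariate list is commonly left to the analysis plan, and an unadjusted primary analysis with an adjusted sensitivity analysis is legitimate. The text never says that covariates are excluded. Nor does it say that reasons for uptake differ by profession; the separate seminars and group discussions do not establish that.

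These arguments limit the size of the point. What remains is that the article names an adjustment for its primary estimate, leaves out covariates that it collects, and uses covariates one sentence later for a secondary analysis.

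**Conclusion.** The point holds in a limited form. As stated, the primary DID is open to bias by two routes: a change in respondent mix that differs by hospital, and profession-specific trends combined with different mixes. Under the assumed inputs the first route gives 0.25 to 2.6 points and the second 1.0 to 1.8, against a 5-point planning effect. The 2.6 needs a 20-point shift in one hospital together with the widest assumed gap. At the planned non-response rate, 0.2 to 0.6 is more realistic for the first route.

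Adjustment is worth making because it costs little and fixes the choice before results are seen. Two further inferences are not supported. One is that adjustment would narrow the interval appreciably; the gain is about 2% in the illustration. The other is that it would make the comparison secure. With one hospital per arm, anything that changes over time in one hospital stays confounded with the intervention, and no individual-level covariate separates the two.

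**What to change.** - Estimate the primary DID from an individual-level model with hospital, survey and hospital-by-survey terms, plus profession, age and gender. Add grouped department only if event numbers allow: 5% of 870 is about 44 baseline events per hospital.
- Report the risk-difference DID standardized to a common staff mix, with the unadjusted DID alongside.
- A main effect for profession deals with changes in mix but not with profession-specific trends. In the first example under (d), the within-hospital changes stay at 2.5 and 1.5 points, so the 1.0-point bias remains. A profession-by-survey term is needed for that route and could be prespecified, at least as a sensitivity analysis.
- Record profession in the three categories of the Study population section. The doctor/nurse parenthesis in the questionnaire description may be only an example, but if taken literally allied staff could not be separated.
- Do not add prior influenza vaccination as a covariate. Baseline uptake is the pre-intervention outcome of the DID, and adjusting for it would condition on that outcome.
- State that the adjustment removes compositional bias only and does not resolve the one-hospital-per-arm confounding.

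The cost is analysis wording and a check of the profession coding. The downside is a slightly more complex model with sparse baseline events.
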